### Randomization

#### Sequence generation

To perform random allocation, permuted block randomization will be used by quadrilateral blocks. Considering the 88-subject sample size, 22 blocks will be generated using a website (www.sealedenvelope.com).

#### Allocation concealment mechanism

In order to blind all the investigators and participants, an individual not involved in the trial will make a randomized list assignment for the participants in each group and will label all the identical containers (in appearance and color) based on their numbers. Therefore, the participants will be unaware of the type of the intervention they receive. The random sequence will be unpredictable, as well.

The 88 participants will be allocated into four groups at a 1:1:1:1 ratio, as follows:Receiving a vitamin D placebo soft gel containing paraffin (weekly) along with one capsule of synbiotic placebo containing 500 mg maltodextrin (daily) for 8 weeksReceiving a 50,000 IU vitamin D soft gel (weekly) along with one capsule of synbiotic placebo containing 500 mg maltodextrin (daily) for 8 weeksReceiving a vitamin D placebo soft gel containing paraffin (weekly) along with a 500 mg synbiotic capsule (daily) for 8 weeksReceiving a 50,000 IU vitamin D soft gel (weekly) along with a 500 mg synbiotic capsule (daily) for 8 weeks

The synbiotic capsules (GeriLact) will contain seven bacteria species (*Bifidobacterium longum* 3.5 × 10^9^ colony-forming units [CFU], *Lactobacillus casei* 3.5 × 10^9^ CFU, *Lactobacillus acidophilus* 10^9^ CFU, *Bifidobacterium breve* 10^10^ CFU, *Lactobacillus rhamnosus* 7.5 × 10^8^ CFU, *Lactobacillus bulgaricus* 10^8^ CFU, and *Streptococcus thermophilus* 10^8^ CFU per 500 mg), and 38.5 mg fructooligosaccharide. They will be manufactured by ZistTakhmir Co., Tehran, Iran. In addition, the placebo capsules with 500 mg maltodextrin content will be provided by the same appearance and color as the synbiotic supplement. Vitamin D soft gels and placebos containing paraffin will be produced by Zahravi, Iran. All the supplements will be placed in identical containers. The participants will be instructed to use the products. At the end of weeks 4 and 8, they will be asked to return the empty containers in order to count the number of remaining supplements for compliance assessment. The participants will also be contacted during the study to check their tolerance and to record the possible side effects of the supplements.

#### Outcome measures

The primary outcome of the study will be the assessment of the intestinal microbiome and the secondary outcomes will include muscle strength, muscle function, and body composition.

At the beginning of the study, the demographic information will be gathered during an interview. In order to assess the dietary intake and compliance through the study, a three-day dietary recall questionnaire (including one weekend day and two weekdays) will be completed by a trained nutritionist at baseline and at the end of the intervention. Nutrient analysis will also be performed by Nutritionist IV software (First Databank, San Bruno, CA) modified for Iranian foods. Moreover, physical activity levels will be assessed by the short form of the International Physical Activity Questionnaire (IPAQ) at the beginning and end of the study. To evaluate sun exposure quantitatively, use will be made of the questionnaire in the research performed by Nikooyeh et al. [25]. It should be noted that the participants will be asked to maintain their usual diets and physical activities during the intervention.

Anthropometric measurements will be determined at baseline and eight weeks after the intervention. Body weight will be measured by minimal clothing and without shoes using a Seca scale with the accuracy of 0.1 kg. Height assessment will be done by a wall stadiometer with the precision of 0.1 cm without shoes. Then, BMI will be calculated as weight in kilograms divided by height in meters squared. Additionally, waist circumference will be measured in the narrowest area above the iliac crest using a flexible tape meter with the accuracy of 0.1 cm.

Body composition including total body, arm and leg lean tissue mass, fat-free mass (FFM), total body fat mass (FM), bone mineral content (BMC), visceral fat area (VFA), and protein content will be determined using a segmental multi-frequency Bioelectrical Impedance Analysis (BIA) InBody S10 analyzer (BioSpace Co., Ltd., South Korea) at the beginning of the study and after the intervention. To obtain the appendicular skeletal muscle mass (ASM), the sum of arms’ and legs’ muscle mass will be calculated. Besides, skeletal muscle mass index (SMI), as an indicator of sarcopenia, will be computed via dividing ASM by height in meters squared.

Upper and lower muscle strengths will be assessed based on handgrip and knee extension strengths using a dynamometer at the beginning and end of the study. Handgrip strength (HGS) will be evaluated for each participant by squeezing a hydraulic hand dynamometer (model MSD, Sihan, Korea) three times in seated position with 1-min intervals. The highest attempt of the dominant hand will be considered for the subsequent analyses. Knee extension strength will be measured in the dominant foot using a portable handheld dynamometer (Digital Force Gauge: SF-500, China) three times with 1-min intervals to rest in the seated position. The three values will be recorded, and the maximum will be defined as the knee extension strength. All the values will be expressed in kilograms.

Physical performance will be characterized using Timed Get-Up-and-Go (TGUG) test. The test will be started at the word “go” and the participants will be required to stand up, walk over a 3-m distance, turn around, walk back, and sit down. The time will be recorded by a chronometer and TGUG will be reported in meters per second. To prevent the measuring error, all strength and performance variables will be determined by one person. All the measurements will be made at the beginning and end of the study.

At baseline and end of the eighth week, stool samples will be collected and transferred to the laboratory using ice packs. The samples will be stored at – 80 °C until analysis. Favorgen Biotech stool mini kit (Favorgen Biotech Corp., Taiwan) will be used for fecal DNA isolation. In addition, real-time polymerase chain reaction (PCR) will be done for quantifying Bifidobacterium, Enterococcus, Firmicutes, Bacteroidetes, and Lactobacillus. The required primers (forward and reverse primers) and probe sequences [26] for the five real-time PCR assays have been provided in Table 1.

**Table 1 Tab1:** Primers and probes for detection of Bifidobacterium, Enterococcus, Firmicutes Bacteroidetes, and Lactobacillus

Targets	Primer and probe sequences
Bifidobacterium	FP: GCGTGCTTAACACATGCAAGTC RP: CACCCGTTTCCAGGAGCTATT Probe: TCACGCATTACTCACCCGTTCGCC
Enterococcus	FP: AGAAATTCCAAACGAACTTG RP: CAGTGCTCTACCTCCATCATT Probe: TGGTTCTCTCCGAAATAGCTTTAGGGCTA
Firmicutes	FP: GTCAGCTCGTGTCGTGA RP: CCATTGTAKYACGTGTGT Probe: GTCAANTCATCATGCC
Bacteroidetes	FP: AGCAGCCGCGGTAAT RP: CTAHGCATTTCACCGCTA Probe: GGGTTTAAAGGG
Lactobacillus	FP: TACATYCCAACHCCAGAACG RP: AAGCAACAGTACCACGACCA Probe: AAGCCATTCTTRATGCCAGTTGAA

*FP* forward primer, *RP* reverse primer

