### Sample size

Due to the fact that the primary outcome of the research is gut microbiome assessment, the sample size was determined according to the study carried out by Most et al. [24], which evaluated gut microbiota composition in relation to the metabolic response to polyphenol supplementation in overweight individuals. Using the Standard Deviation (SD) of the logarithm of Firmicutes from that study (0.32), considering a difference equal to 1.25 SD (0.32 units of change in the logarithm of Firmicutes) between the two groups with the lowest and highest values of Firmicutes, and considering *α* = 0.05, *β* = 0.10, and a 10% dropout, a 22-subject sample size was estimated for each group. In total, 88 overweight and obese middle-aged women will be enrolled.

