#### Statistical analysis

Statistical analysis of the data will be performed using the SPSS 22.0 software (SPSS Inc., Chicago, IL). Initially, the Shapiro–Wilk test will be used for the evaluation of normality. The data will be reported as percentages for qualitative variables and mean ± SD for quantitative variables. Categorical variables will be compared using chi-square test. In addition, the baseline mean differences will be assessed using the analysis of variance (ANOVA). For assessing pairwise differences between the study groups, Tukey’s post-hoc test will be performed. Analysis of covariance (ANCOVA) will also be used to evaluate the intervention effects between the study groups with adjustment for baseline values. A logarithmic correction will be done for skewed data before analysis. Moreover, paired-sample *t*-test and Wilcoxon test will be used to compare the mean values of normally distributed and skewed data within groups after the intervention. To analyze the microbiome data, the fold expression change will be calculated. It should be noted that at 10% or higher dropouts, the intention to treat (ITT) analysis will be conducted. *P* < 0.05 will be considered statistically significant.

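### The primary outcome is left as five taxa under one 0.05 threshold while the trial is sized on Firmicutes alone, and two of the five are genera supplied in the capsule

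*Protocol article*

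**What the plan says.** Under Outcome measures, the protocol article says: "The primary outcome of the study will be the assessment of the intestinal microbiome". The same section later says that real-time PCR "will be done for quantifying Bifidobacterium, Enterococcus, Firmicutes, Bacteroidetes, and Lactobacillus". None of the five is singled out, and no composite or order of testing is given.

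Under Sample size, one of the five is used: "Using the Standard Deviation (SD) of the logarithm of Firmicutes from that study (0.32"), with alpha 0.05, power 90% and 10% dropout, giving 22 per group and 88 in all. That section also calls the primary outcome an assessment of the gut microbiome, without declaring Firmicutes to be it.

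Under Statistical analysis:
- On treatment effects: "Analysis of covariance (ANCOVA) will also be used to evaluate the intervention effects between the study groups with adjustment for baseline values".
- On multiple comparisons: "For assessing pairwise differences between the study groups, Tukey’s post-hoc test will be performed".
- On the threshold: P "< 0.05 will be considered statistically significant".
- Microbiome data are to be expressed as a fold change.

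Under Allocation concealment mechanism: "The synbiotic capsules (GeriLact) will contain seven bacteria species". The list gives two Bifidobacterium species, four Lactobacillus species and Streptococcus thermophilus, together with fructooligosaccharide. Stool is collected at baseline and when the eight weeks of dosing end.

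**The concern.** The primary outcome names a field of measurement, not a variable. Five assays fit the description, and the protocol does not say which of them decides the primary objective. The sample size points to Firmicutes, but a reader of the results could accept any significant taxon as an effect on the microbiome. Tukey's procedure covers the comparisons between groups within one taxon; it does nothing across taxa. Read that way, the 5% error rate for the primary claim is not held, and the choice of lead taxon could be made after the data are seen.

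There is a separate question of interpretation. Two of the five targets are genera that the synbiotic groups swallow daily until the final stool sample. PCR quantifies DNA of the genus, whatever its source. If one of these two taxa carries the primary claim, the result may not mean what the rationale in the Background needs, which is a change in the gut microbiome that could mediate effects on muscle.

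**Working it through.** **1. The plan's own figure.** Inputs from Sample size: difference 1.25 SD between the extreme groups, alpha 0.05, power 0.90, dropout 10%, four groups.
- One-way ANOVA, two groups at the extremes and two at the mean: noncentrality = n × d² / 2. With d = 1.25 and n = 20 this is 20 × 1.5625 / 2 = 15.6, and power is 0.914. With n = 19 power is 0.897, so 20 evaluable are needed.
- Dropout: 20 × 1.1 = 22, the stated figure. Dividing instead gives 20 / 0.9 = 22.2, rounded up to 23.

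The 22 per group is therefore reproduced as a single four-group test of one variable, log Firmicutes, at 0.05. It contains nothing for the other four taxa.

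**2. Error rate over five taxa.** Assumption: each taxon has one four-group test at 0.05, and any one significant result is read as a microbiome effect.
- Independent tests: 1 − 0.95⁵ = 0.226.
- Correlated tests, simulated as five four-group F tests with 20 per group, equal correlation, no treatment effect and 20,000 runs:

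| Correlation | Chance of at least one P < 0.05 |
|---|---|
| 0.3 | 20.8% |
| 0.5 | 18.5% |
| 0.7 | 15.4% |
| 0.9 | 10.8% |

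The simulation leaves out the baseline covariate. The correlations are assumed, since the protocol gives none. Simulation error is about 0.2 to 0.3 percentage points.

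**3. Capsule content.** Inputs from the list under Allocation concealment mechanism, in CFU per capsule.
- Bifidobacterium: 3.5×10⁹ + 1×10¹⁰ = 1.35×10¹⁰.
- Lactobacillus: 3.5×10⁹ + 1×10⁹ + 7.5×10⁸ + 1×10⁸ = 5.35×10⁹.
- Streptococcus: 1×10⁸.
- Total 1.895×10¹⁰. Share of the first two genera: 1.885×10¹⁰ / 1.895×10¹⁰ = 99.5%.

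**4. Which contrasts are exposed.** Number the groups as listed: 1 double placebo, 2 vitamin D only, 3 synbiotic only, 4 both. Of the six pairs, four set a synbiotic group against a non-synbiotic group (3 v 1, 4 v 1, 3 v 2, 4 v 2) and are exposed to ingested DNA. The two vitamin D contrasts within a synbiotic stratum (2 v 1, 4 v 3) should be balanced for it. The multiplicity problem touches all six.

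**5. Cost of the alternatives.**
- Firmicutes as the single primary at 0.05: 20 evaluable per group, as now.
- Five co-equal primaries with Bonferroni, alpha 0.05 / 5 = 0.01: 27 evaluable per group, 27 / 0.9 = 30 enrolled, 120 in all. With 20 evaluable, power is 0.765. This assumes the Firmicutes effect in SD units for every taxon, because no SD is given for the other four.

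**A related inconsistency.** Sample size equates 1.25 SD with 0.32 log units while giving the SD as 0.32. By its own figures, 1.25 SD is 0.40 and 0.32 is 1.00 SD. At 1.00 SD, 20 evaluable per group give power 0.737 at 0.05, and 0.498 at 0.01. The two statements need reconciling.

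**The case against.** The strongest reply is that the protocol nowhere says success on one taxon meets the primary objective, and that an adjustment across taxa can properly sit in an analysis plan that is not shown. Both parts are true. The error rates above are conditional on that reading, and the lack of an adjustment rule would not be a finding by itself. What remains is on the page: the stated primary outcome covers five measurements and the sized one is a single taxon. A later plan can add a multiplicity rule, but the protocol has not told it which variable is primary.

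A second reply is that 22.6% is an upper figure. That also stands. Lactobacillus and Enterococcus belong to the phylum Firmicutes (general taxonomy, not stated in the protocol), so the five results are unlikely to be independent. The rate falls with correlation but is still about twice the nominal level at 0.9.

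On the capsule, a reader might infer that a rise in Bifidobacterium and Lactobacillus is to be expected from product passing through, and might put a log10 size on it. The documents do not support this. It would need stool mass, DNA recovery and resident density, and none is given. A reader might equally want any such rise labelled as product recovery. That is no better founded, because the capsule also contains fructooligosaccharide, which may act on resident bacteria, and the assay cannot separate the sources. The objective as written also speaks only of the intestinal microbiome and makes no claim of colonisation.

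**Conclusion.** The concern holds in two parts of unequal weight.

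The main part is that the protocol does not fix its primary outcome. It names five measurements by implication, sizes on one, and applies a single 0.05 threshold. If any significant taxon is taken as a microbiome effect, the familywise error is 22.6% under independence and about 11% to 21% for correlations of 0.9 to 0.3. This rests on one omnibus test per taxon and on that reading of success.

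The second part is a caution about interpretation. Two of the five targets are genera making up 99.5% of the capsule's CFU, and sampling coincides with the end of dosing. In synbiotic versus non-synbiotic contrasts, a rise in either could partly reflect ingested DNA. How much cannot be derived from the documents. It does not follow that the trial's microbiome result will be an artefact, and the vitamin D contrasts within a synbiotic stratum are not drawn into it.

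**What to change.** - In Outcome measures, declare one primary outcome: log Firmicutes at week 8, adjusted for baseline by ANCOVA across the four groups, tested at 0.05. This is the variable the trial is already sized on.
- In Statistical analysis, reconcile this with the fold-change wording, so that one scale is defined for the primary analysis.
- Make Bifidobacterium, Enterococcus, Bacteroidetes and Lactobacillus secondary, with Holm adjustment over the four (smallest P value against 0.05 / 4 = 0.0125).
- State that a higher Bifidobacterium or Lactobacillus signal in the synbiotic groups cannot distinguish ingested from resident bacteria, and does not by itself establish a change in the resident microbiome.

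This returns the error rate of the primary claim to 5% and leaves the sample size where it is at 1.25 SD. It needs no new assays. The cost is that four taxa lose primary status and the registry entry must be updated. Naming Firmicutes settles the error rate but does not resolve the source of bacterial DNA: the capsule's Lactobacillus and Streptococcus fall within that phylum too, and their contribution to it is equally undetermined by the documents.

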#### Statistical analysis

Statistical analysis of the data will be performed using the SPSS 22.0 software (SPSS Inc., Chicago, IL). Initially, the Shapiro–Wilk test will be used for the evaluation of normality. The data will be reported as percentages for qualitative variables and mean ± SD for quantitative variables. Categorical variables will be compared using chi-square test. In addition, the baseline mean differences will be assessed using the analysis of variance (ANOVA). For assessing pairwise differences between the study groups, Tukey’s post-hoc test will be performed. Analysis of covariance (ANCOVA) will also be used to evaluate the intervention effects between the study groups with adjustment for baseline values. A logarithmic correction will be done for skewed data before analysis. Moreover, paired-sample *t*-test and Wilcoxon test will be used to compare the mean values of normally distributed and skewed data within groups after the intervention. To analyze the microbiome data, the fold expression change will be calculated. It should be noted that at 10% or higher dropouts, the intention to treat (ITT) analysis will be conducted. *P* < 0.05 will be considered statistically significant.

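### Before-after tests within each arm share the P < 0.05 rule with the between-group ANCOVA and are not marked as descriptive

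*Protocol article*

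**What the plan says.** All of the following is in the protocol article.

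- **Statistical analysis, between groups.** ANCOVA "will also be used to evaluate the intervention effects between the study groups with adjustment for baseline values". Earlier in the same section, directly after the baseline ANOVA: "For assessing pairwise differences between the study groups, Tukey’s post-hoc test will be performed".
- **Statistical analysis, within groups.** After the ANCOVA sentence and a sentence on log-transforming skewed data, the plan adds that the paired t-test and the Wilcoxon test "will be used to compare the mean values of normally distributed and skewed data within groups after the intervention".
- **Statistical analysis, threshold.** The section closes with one rule for everything: P "< 0.05 will be considered statistically significant". No test is exempted or ranked below another.
- **Allocation concealment mechanism.** "The 88 participants will be allocated into four groups at a 1:1:1:1 ratio". The first group receives both placebos; the other three receive vitamin D, synbiotic, or both.

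**The concern.** The trial asks what the supplements do. A before-after test in one arm asks whether that arm changed over eight weeks, for whatever reason. Several other sources of change are plausible here:

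- Handgrip, knee extension and the timed get-up-and-go are effort tests done twice, so familiarity can move all arms.
- Women enter on a BMI of at least 25, so weight-related measures can regress to the mean.
- Diet, activity and sun exposure can shift. The Objectives section has these recorded at both time points to control confounding, but a paired test adjusts for none of them.

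Randomisation removes such shared changes only when arms are compared with each other. A P value below 0.05 in one arm and above it in another is not a test of the difference between them.

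At stake is the reporting. With four arms, five bacterial targets and many secondary measures, some supplemented arm may well show a significant change while double placebo does not. The plan as written would let that stand beside a null ANCOVA at the same threshold, with no rule on which one decides.

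**Working it through.** **The plan's own figure.** The plan gives no error rate for these tests. The one figure needed is the arm size: "a 22-subject sample size was estimated for each group". It reproduces. A four-group ANOVA with extreme groups 1.25 SD apart, the other two at the midpoint, alpha 0.05 and power 0.90 needs 20 evaluable per arm (noncentrality 20 × 1.25² / 2 = 15.6, power 91.4%), and 20 × 1.1 = 22. In reverse, 22 × 0.9 = 19.8, so about 20 per arm are expected to be analysed.

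**Inputs.** Four arms, one of them double placebo; threshold 0.05, taken as two-sided because the document does not say; 20 evaluable per arm. The arms contain different women, so with no real change the four within-arm tests of one outcome are independent.

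**Step 1: each test alone.** For its own question, whether this arm changed, each paired test has a 5% error rate. Nothing is inflated at this point.

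**Step 2: the misleading pattern.** Let q be the probability that an arm's test is not significant, equal in all arms because no supplement works. The pattern is at least one of the three supplemented arms significant and double placebo not:

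P(pattern) = q × (1 − q³) = q − q⁴

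With no change in any arm, q = 0.95, so P = 0.95 × (1 − 0.95³) = 0.95 × 0.1426 = **13.5%** per outcome.

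**Step 3: a common drift in all arms.** Assume the same standardised mean change δ (in SDs of the change) in every arm, and still no supplement effect. The probability p that one paired t-test is significant comes from the noncentral t with 19 degrees of freedom and noncentrality δ√20; q = 1 − p.

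| δ (assumed) | p | q | q − q⁴ |
|---|---|---|---|
| 0 | 0.050 | 0.950 | 13.5% |
| 0.2 | 0.136 | 0.864 | 30.7% |
| 0.3 | 0.247 | 0.753 | 43.2% |
| 0.4 | 0.397 | 0.603 | 47.1% |
| 0.5 | 0.565 | 0.435 | 40.0% |
| 0.6 | 0.721 | 0.279 | 27.3% |
| 0.8 | 0.924 | 0.076 | 7.6% |

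The maximum is where 1 − 4q³ = 0, so q = 0.63 and P = 0.63 − 0.63⁴ = **47%**. It falls again for large drift because double placebo then becomes significant too. With 22 per arm, the values at δ = 0.2, 0.3, 0.4 and 0.5 are 32.2%, 44.6%, 46.4% and 36.7%.

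**Step 4: the ANCOVA under the same conditions.** A simulation with 20 per arm, an assumed pre-post correlation of 0.5 and 8,000 runs per setting gave false-positive rates for the four-group ANCOVA of 4.8%, 5.0%, 5.2% and 5.2% at common shifts of 0, 0.2, 0.3 and 0.45. With this correlation the SD of the change is √(2 − 2 × 0.5) = 1, so the shifts are on the scale of δ. The pattern of Step 2 appeared in 13.9%, 31.4%, 43.1% and 44.3% of the same runs, in line with the formula.

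**The case against.** The strongest reply is that the plan already puts the efficacy question in the right place. ANCOVA is the method named for intervention effects, the within-group tests come after it, and nowhere does the article say that a within-group P value will be read as evidence of a supplement effect. A condensed article may also leave such interpretive wording to an analysis plan that is not shown.

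Most of this stands, and it rules out two stronger readings.

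- A reader might infer that the trial intends to prove efficacy with the paired tests. The text does not support that. The risk is a later misreading that the plan leaves open.
- A reader might also say that the tests themselves have a high false-positive rate, citing 1 − 0.95⁴ = 18.5% for any of four arms, or 1 − 0.95²⁰ = 64% over five targets and four arms. Those figures describe a rule, any arm significant, that the protocol does not contain. The 18.5% includes cases where double placebo is significant, which would support no supplement claim. The 64% assumes independence between targets measured in the same stool samples.

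Participants are also asked to keep their usual diet and activity, so the drift may be small and the rate nearer to 13.5%.

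The reply does not remove the point. The within-group tests are written into the plan, not left to another document. They carry the same threshold as the ANCOVA, and nothing says which result governs.

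**Conclusion.** The point holds as one of interpretation and reporting, of minor to moderate weight. The plan includes tests that cannot isolate a supplement effect and neither marks them as descriptive nor subordinates them to the ANCOVA.

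The 13.5% needs only independent arms and a 5% error rate per test. The higher rates rest on assumed drift sizes, equal in all arms, since the documents give none; 47% is a ceiling and not an estimate. The ANCOVA result of about 5% also rests on the assumed correlation of 0.5 and normal data. All rates are per outcome. Multiplicity over the five targets affects both kinds of analysis and is a separate matter.

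The randomised comparison and the sample size do not depend on the paired tests, which is why the weight is no greater.

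**What to change.** Replace the sentence on the paired t-test and the Wilcoxon test with wording such as this: *Within each arm, the mean change from baseline (on the log scale for skewed variables) will be given with its 95% confidence interval, as description and without P values. Conclusions on the effect of the supplements will rest only on the baseline-adjusted between-group ANCOVA and its multiplicity-adjusted pairwise contrasts.*

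This also settles two smaller ambiguities. The present sentence has a Wilcoxon test comparing means, which it does not do, on skewed data that the preceding sentence says will be log-transformed. And the Tukey sentence follows the baseline ANOVA, so it is unclear whether it covers the outcome contrasts.

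If the investigators prefer to keep the tests, the minimum is to label them descriptive and add the second sentence above.

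The cost is two sentences, settled before unblinding. Design, sample size and data collection do not change. The only loss is that within-group P values, customary in this field, would no longer be reported.

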### Participants

The study will be performed on 88 overweight and obese women (body mass index (BMI) ≥ 25 kg/m^2^) aged 40–55 years, having insufficient vitamin D intake, not having taken vitamin D supplements orally or by injection during the past 2–3 months, not having reached menopause, not having taken synbiotic, probiotic, and prebiotic supplements during the past 2–3 months, not having the indications of chronic diseases such as diabetes, cardiovascular disease (CVD), uncontrolled blood pressure, and liver and kidney disorders, not taking supplements containing vitamins, minerals, and omega-3 or fish oil, not having taken antibiotics during the past 3 weeks, not following a special diet, not having used the medications that affect weight over the past 2 months, and not having used steroidal and non-steroidal anti-inflammatory drugs, anticonvulsants, anti-cholesterol drugs, antacids, diuretics, and laxatives over the past 2 months. The exclusion criteria will consist of being influenced by any acute diseases during the study, being less than 90% compliant with the intervention, and not being willing to continue the study.

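### Intention-to-treat analysis is made conditional on 10% dropout, no analysis set is named below that, and the implied set is compliant completers

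*Protocol article*

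**What the plan says.** The Statistical analysis section of the protocol article has one sentence on the analysis population: "It should be noted that at 10% or higher dropouts, the intention to treat (ITT) analysis will be conducted". It does not say who is analysed when dropout is lower, and it does not define dropout.

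The Participants section gives as exclusion criteria "being influenced by any acute diseases during the study, being less than 90% compliant with the intervention, and not being willing to continue the study". None of these can be known before a woman is randomised and has started her supplements. Compliance is measured during follow-up: under Allocation concealment mechanism, women at weeks 4 and 8 are to "return the empty containers in order to count the number of remaining supplements for compliance assessment".

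The Sample size section plans for "a 10% dropout, a 22-subject sample size was estimated for each group", and allocation is stated as "The 88 participants will be allocated into four groups at a 1:1:1:1 ratio". The planned dropout rate and the trigger for intention to treat are therefore the same figure.

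**The concern.** An analysis of all women as randomised keeps the groups comparable. Here it is promised only when enough women are lost. Three things are wrong with that.

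- The population for the primary microbiome comparison, and for every secondary outcome, depends on something observed after randomisation.
- The rule runs the wrong way. With few losses, intention to treat needs the fewest assumptions about missing values, yet on the plain reading that is when it is not done.
- The trigger sits where the sponsor expects dropout to be, so one woman more or less can decide which population is reported.

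Women who miss doses, fall ill or withdraw may differ between active and placebo groups. The protocol itself plans to record tolerance and side effects. If such women are removed, a difference between groups can reflect who was removed and not what the supplements did.

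**Working it through.** **Inputs.** From the protocol article: 88 women, 22 per group, 10% planned dropout, trigger at 10% or more, 90% compliance limit, design difference 1.25 SD. Assumed here, because the article gives no figure: the true dropout rate (5% to 20%) and the gap in mean outcome between removed and retained women (0.25 to 1 SD).

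**The plan's own figure.** A four-group one-way analysis of variance with the two extreme means 1.25 SD apart and the other two midway, α = 0.05 and 90% power, needs 20 per group (power 0.914). Then 20 × 1.10 = 22, the stated size. (Dividing by 0.90 gives 22.2, so 23.) The 10% is thus the planning allowance for dropout, and it reappears as the trigger.

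**Where the rule switches.** 0.10 × 88 = 8.8, so the trigger is 9 losses: 8/88 = 9.1% gives no intention-to-treat analysis and 9/88 = 10.2% gives one.

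**How likely the switch is.** With the number lost X distributed as Binomial(88, p), the chance of triggering is P(X ≥ 9):

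| True dropout p | P(X ≥ 9) |
|---|---|
| 5% | 0.03 |
| 8% | 0.27 |
| 10% (planned) | 0.52 |
| 12% | 0.74 |
| 15% | 0.93 |
| 20% | 0.995 |

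**What removal can do to a contrast.** Let f be the fraction of an arm removed and g the gap (removed minus retained mean). The full-arm mean equals the retained mean plus f × g, so removal shifts that arm's mean by −f × g. For arms A and B the size of the bias is |f_A × g_A − f_B × g_B|. With 8 losses, just under the trigger, and the same gap in both arms:

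| Losses in the two arms compared | Gap 0.25 SD | Gap 0.5 SD | Gap 1 SD |
|---|---|---|---|
| 2 of 22 and 2 of 22 | 0 | 0 | 0 |
| 5 of 22 and 0 of 22 | 0.06 SD | 0.11 SD | 0.23 SD |
| 8 of 22 and 0 of 22 | 0.09 SD | 0.18 SD | 0.36 SD |

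The last row is the extreme: 8/22 = 0.364, and 0.364/1.25 is 29% of the design difference.

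**How easily the compliance limit is crossed.** One weekly soft gel for 8 weeks is 8 doses; one missed dose leaves 7/8 = 87.5%, below 90%. One capsule daily is 56 doses; six missed leave 50/56 = 89.3%, also below 90%. The article does not say whether compliance is judged per product or pooled, nor whether women removed for it count towards the 10%. If they do not, removals could exceed 8 without triggering intention to treat, and the last row of the table would no longer be the extreme.

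**The case against.** The strongest reply is that the completer default is inferred. The Statistical analysis section names no set below 10% and does not say that intention to treat replaces another analysis; it could be an addition when attrition matters. The Participants section does not say in words that excluded women's data leave the analysis. This stands as a point of precision, and a reader should not report that the protocol states a per-protocol primary analysis. It does not rescue the rule: on either reading no commitment is made to analyse all randomised women, and the main set remains unnamed.

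A reader might also infer that the population is picked from the trial's results. The documents do not support that. The trigger is the overall dropout rate, fixed in advance, in a double-blind trial with identical containers. A given count selects one branch, and discretion enters only through the undefined term dropout.

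A further fair point is that near-even odds hold only if true dropout is close to 10%; at 5% or 20% the branch is almost certain. Nor is the shift in a single arm's mean the bias: at 8/88 = 9.1% removed and a 1 SD gap that shift is about 0.09 SD, but equal removals with equal gaps cancel in the contrast.

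Finally, an article may leave the choice of missing-data method to a fuller document. That is accepted and is not part of this point. Condensing may explain silence, but the conditional rule is stated.

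**Conclusion.** The point holds as a badly fixed rule. Intention to treat depends on observed dropout, the set used otherwise is unnamed, and the conditional wording together with the post-randomisation exclusions points to compliant completers. At the sponsor's own dropout assumption the chance of each branch is about one half (0.52 against 0.48).

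The possible bias is 0 when removals and gaps are balanced across arms, and about 0.36 SD at the extreme of 8 losses in one arm with a 1 SD gap. The gap and the split are illustrations, not predictions, and nothing in the article shows that a material distortion will occur. The case for change rests on the rule itself: it gives up a protection that costs little to keep, and it leaves its own trigger undefined.

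**What to change.** Replace the conditional sentence in Statistical analysis with: *The primary analysis includes all randomised women in their allocated group, whatever the dropout or compliance; an analysis restricted to women with at least 90% compliance is a sensitivity analysis.*

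In Participants, state that the three criteria arising during the study do not remove randomised women from the primary analysis, and that the week-8 measurements already planned are still sought, where women agree, from those who stop or are non-compliant. Say whether the 90% applies to each product or to both together, so that the sensitivity set is defined.

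The cost is a few sentences, some effort to obtain week-8 stool samples and muscle measurements from women who have stopped, some dilution of the effect by non-compliers, and a few missing week-8 values to handle. Including all randomised women removes the bias above only as far as those values are obtained; the remainder rests on whatever missing-data method is chosen. The sample size stays at 22 per group, 88 in all. The change should be made before outcome data are seen.
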